## 5.0 COMMUNITY SURVEYS

In the community surveys, 200 households will be recruited from a list randomly generated from a census database. The community surveys will consist of three components: (1) a household survey consisting of a questionnaire administered to heads of households, (2) women’s survey consisting of a questionnaire administered to all women of child-bearing age (15-49 years), and (3) clinical surveys consisting of biomarker testing of all children under fifteen years of age, and of one household member within the age category: 15-24 years, 25-34 years, 35-44 years, 45-54 years, and > 55 years.

## 5.1 Household survey

### 5.1.1 Selection of households

A sample of 200 residential households will be selected in each site. In order to create a sampling frame for the selection of participating households, all residential households within each of the three sites have been enumerated and mapped prior to the onset of the surveys as part of a separate protocol. A random sample of households will be selected from each site using computer-generated random numbers to generate a list of households to be approached. Study personnel will conduct door-to-door recruitment to identify those households with at least one adult household resident in sequential order according to the recruitment list. Households without a child of appropriate age will be removed from the recruitment list. Residents not home during the initial contact will be re-visited on at least three other occasions before eliminating them from our sample selection process. New recruitment lists will be randomly generated for each survey using replacement.

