| Participants and Sample Size | **Community survey:**  Household survey,:  - randomly sample 200 households per site  - administer a household questionnaire to the head of the household or their designate.  Women’s survey:  - sample all women in the reproductive age group (15 – 49 years) in each selected household.  - administer a women’s questionnaire to all selected women  Clinical survey:  **-** sample all children under fifteen years of age in each selected household  - randomly sample one household member within the age category 15-24 years, 25-34 years, 35-44 years, 45-54 years, and > 55 years.  - collect a fingerprick blood sample from each participant for measurement of hemoglobin, thick and thin blood smear, rapid diagnostic test (RDT) for malaria, and filter paper blood sample  **School survey:**  - randomly select 3 primary schools per site.  - randomly select 100 pupils per school (30 children from each of the classes 2-6) |

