# 4.0 STUDY METHODS

## 4.1 Overall study design

We propose to conduct cross-sectional surveys in communities and primary schools twice a year for at least 2 years in the 3 different sites. The surveys will be timed to correspond to the high and low malaria transmission seasons, when possible. In the community surveys, 200 households will be recruited from a list randomly generated from a census database at each site. The community surveys will consist of three components: (1) a household survey targeting heads of households, (2) a women’s survey targeting all women of child-bearing age (15-49 years), and (3) clinical surveys of all children under fifteen years of age, and of one household member within the age category 15-24 years, 25-34 years, 35-44 years, 45-54 years, and > 55 years. The clinical surveys will include a fingerprick blood sample for measurement of hemoglobin, thick and thin blood smear, rapid diagnostic test (RDT) for malaria, and filter paper blood sample. The school surveys will be conducted in 3 randomly selected primary schools per site. A total of 100 randomly selected children will be recruited in each school. The school surveys will include only the clinical assessments including measurement of temperature, and a fingerprick blood sample for measurement of hemoglobin, thick and thin blood smear, RDT for malaria, and filter paper blood sample.

##

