### 5.1.2 Screening of respondents.

When a household with at least one household adult resident is identified, study personnel will briefly describe the purpose of the study to the head of the household or any adult household member present at home in the appropriate language (usually Luganda or Lusoga for those in Walukuba; Rukiga or Runyankore for those in Kihihi, and Japadhola and Ateso for those in Nagongera sub-county). The inclusion criteria are: 1) Usual resident who is present in the sampled household on the night before the survey, 2) adult aged 18 years or older, 3) agreement to provide informed consent. The exclusion criterion are: 1) no adult resident home on more than 3 occasions, 2) household vacant, 3) dwelling destroyed or not found

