# STATISTICAL ISSUES

## 8.1 Outcome measures

| Outcome | Definition |
| --- | --- |
| Prevalence of anemia | Proportion of Hb measurements < 11.0 g/dL. Anemia will be classified according to severity: mild (Hb 8.0 – 10.9), moderate (Hb 5.0 – 7.9), severe (Hb < 5.0). |
| Parasite prevalence | Proportion of study participants with a positive thick blood smear at the time of assessment |
| IRS coverage | Proportion of households sprayed |
| ITN coverage. | - Percentage of household with at least one bednet  - Percentage of household with at least one ITN  - Average number of nets per household  - Average number of ITNs per household  - Percentage of children age who slept under any net the prior night  - Percentage of children age who slept under an ITN the prior night  - Percentage of pregnant women who slept under any net the prior night  - Percentage of pregnant women who slept under an ITN the prior night |
| IPT coverage | Percentage of pregnant women on intermittent antimalarial treatment or antimalarial chemoprophylaxis |
| ACT’s coverage | Proportion of febrile episodes in children treated with an ACT |
| Prompt effective treatment of fever | Proportion of children with fever treated within 24 hours of onset of symptoms with an ACT |
| Under five Crude Death Rate (all cause mortality) | The number of children who die by the age of five, per thousand live births. |
| Under five malaria mortality rate | Proportion of deaths in children under five attributed to malaria per thousand live births. |
| Prevalence of malaria specific immune responses | Proportion of study participants with malaria specific immune responses at the time of assessment  Antibody density in participants at the time of assessment |

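### Section 5.1.1 strikes households without a child of an undefined age from the random list, contradicting the stated exclusions and narrowing the household, women's, adult and absolute mortality estimates

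*Protocol*

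**What the plan says.** Section 4.1 states the design without any condition on children: "200 households will be recruited from a list randomly generated from a census database at each site". The Study Summary agrees ("randomly sample 200 households per site"), and so does Section 5.0. Section 5.1.1 explains that the frame is complete, because "all residential households within each of the three sites have been enumerated and mapped prior to the onset of the surveys".

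The same section then adds a filter: "Households without a child of appropriate age will be removed from the recruitment list". No section says which age is meant. The household exclusions in Section 5.1.2, repeated in the Study Summary, are only these: "1) no adult resident home on more than 3 occasions, 2) household vacant, 3) dwelling destroyed or not found".

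This one list feeds every community component. Women are recruited from each household in the household survey (5.2.1), and their interviews give the birth histories and lead to the verbal autopsies (5.2.4, 5.2.5). Adults for blood sampling come from the same households (5.3.1, 5.3.2). Section 8.1 defines the outcomes without limiting them to households with children, for example "Percentage of household with at least one ITN" and, for all-cause mortality, "The number of children who die by the age of five, per thousand live births".

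**The concern.** There are two separate problems.

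First, the protocol gives two incompatible selection rules. A team working from 5.1.2 or the Study Summary would enrol a household without children. A team working from 5.1.1 would not. Practice could differ between sites or survey rounds.

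Second, the filter changes the population if 5.1.1 is followed. Household net ownership, spraying coverage, preventive treatment and net use in pregnancy, and adult parasitemia, anemia and serology would describe only households with children. A woman in her first pregnancy with no child at home, for instance, is lost from the pregnancy indicators. For mortality, the filter acts partly on the outcome itself: a household that lost its only eligible child is dropped because of that death.

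Removed households give no questionnaire, birth history or blood sample. Weighting cannot represent units whose selection probability is zero, so an analysis plan cannot repair this afterwards.

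**Working it through.** **The plan's own figures.** Section 8.2 expects 200 × 1.5 = 300 children aged 6–14 per community survey; this reproduces. The malaria mortality inputs there (6.5, 12.9 and 19.4 per 1000, at attributable shares of 20%, 40% and 60%) imply 6.5/0.20 = 32.5, 12.9/0.40 = 32.25 and 19.4/0.60 = 32.3 per 1000. The implied all-cause figure is therefore about 32.3 per 1000 at every site.

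**Coverage.** Let s be the share of households with no eligible child, and c1 and c0 the coverage with and without children. The target is (1 − s)c1 + s·c0, but the filtered sample estimates c1, so the bias is s × (c1 − c0). The document gives neither s nor the gap. Assumed ranges:

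| s | gap 5 points | gap 10 points | gap 20 points |
|---|---|---|---|
| 10% | 0.5 | 1.0 | 2.0 |
| 20% | 1.0 | 2.0 | 4.0 |
| 30% | 1.5 | 3.0 | 6.0 |

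For comparison, the 95% half-width at n = 200 and 50% coverage is 1.96 × √(0.25/200) = 6.9 points. The sign depends on which kind of household has the higher coverage.

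**Mortality: share of deaths lost.** Suppose a household has k children in the eligible age range, each having died independently with probability p, and drops out only if all have died. With w_k the share of households with k such children, the share of deaths lost is Σ w_k·k·p^k / Σ w_k·k·p. The weights below are illustrative, since the document has no family-size data.

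- *Under 15*, k = 1/2/3/4 with weights 0.1/0.1/0.2/0.6. At p = 0.0323: (0.1 + 0.2p + 0.6p² + 2.4p³)/3.3 = 3.2%. At p = 0.10: 3.9%.
- *Under five*, k = 1/2/3 with weights 0.3/0.5/0.2. At p = 0.0323: (0.3 + 1.0p + 0.6p²)/1.9 = 17.5%. At p = 0.10: 21.4%.
- *Under five*, weights 0.5/0.4/0.1. At p = 0.0323: (0.5 + 0.8p + 0.3p²)/1.6 = 32.9%. At p = 0.10: 36.4%.

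The result depends far more on the age reading and the family sizes than on p.

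**Mortality: effect on the rate.** If a share f of deaths is lost and those births also leave the denominator, the observed rate is q(1 − f)/(1 − qf). With q = 32.3 per 1000, f = 3% gives 31.4 (−2.9%) and f = 4% gives 31.0 (−3.9%). Larger assumed losses of 10%, 20% and 30% give 29.2, 26.0 and 22.8.

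**Which births are counted.** The last formula assumes that only the lost deaths leave the data. Section 5.2.4 asks about each child a woman has borne and states no time limit. On the under-five reading, a household whose children all survived past five, with no younger child, is removed too. If those older births enter the estimate, survivors leave the denominator and the direction is no longer fixed. On the under-15 reading this arises only for births more than 15 years back.

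**What is not affected.** On the under-15 reading, removed households contain no children who could enter child parasitemia, child anemia, child net use or ACT coverage, nor the school–community comparison at ages 6–14. Those outcomes are not biased.

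**The case against.** The strongest reply is that the sentence may be a leftover. The Study Summary, 4.1, 5.0 and 5.1.2 all omit it, and the protocol does not show which version would be used. That is a reason to reconcile the sections; it does not remove the conflict. It does mean that the bias is conditional on the rule being applied.

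A second reply concerns mortality. A reader might infer that between a fifth and a third of under-five deaths disappear. The document does not support this. Those figures need the under-five reading, whereas the clinical survey recruits all children under fifteen (4.1, 5.3.1, 5.3.2) and no recruitment criterion uses under five. They also rest on assumed family sizes, and they ignore older siblings and other women's children in the home, either of which could keep the household in. This reply stands.

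Third, the primary mortality metric in Section 8.2 is relative change from year to year. A stable loss largely cancels there, so the exposure is mainly in the absolute rates of objectives 3 and 4. This also stands.

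Fourth, the coverage bias is built from assumptions, and even its upper end lies within the sampling half-width of one survey. That is true, but a selection bias recurs in every survey and does not shrink as surveys accumulate.

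**Conclusion.** The point holds as a contradictory and undefined selection rule that should be fixed before fieldwork. If it is applied, household net ownership, spraying coverage, women's indicators and adult parasitemia, anemia and serology describe only households with children, which Section 8.1 does not intend. The coverage bias is 0.5–6 points under the assumed ranges, in an unknown direction.

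Absolute under-five mortality is exposed to a lesser or less certain degree. If the age means under 15, the better supported reading, the bias is downward and probably small: about 3–4% of deaths under the illustrative family sizes. If it means under five, the loss could be much larger, but neither its size nor its direction can be settled without knowing which births enter the estimate.

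It would go too far to say that all of objective 5, or the parasite-rate comparison with schools, is estimated for the wrong population. On the under-15 reading the outcomes with child denominators are sound, and year-to-year relative mortality is less affected if the loss is stable.

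**What to change.** Delete the sentence, so that 5.1.1 matches 5.1.2 and the Study Summary. Give the household and women's questionnaires, and do the adult sampling, in the first 200 consenting households in list order, whether or not a child lives there.

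If children aged 6–14 then number fewer than 300, choose one of two courses in advance:

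- restate the figure in Section 8.2 and its precision; or
- continue down the same list to households with children and use these only for child outcomes, keeping them out of the household coverage, women's, mortality and adult parasitemia, anemia and serology estimates.

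The cost is fewer children or more visits. Section 8.2 does not say whether its 1.5 children per household presumes the filter. If it does, and 10–30% of households have no eligible child, 200 unfiltered households yield 200 × 0.9 × 1.5 = 270 down to 200 × 0.7 × 1.5 = 210 children. Making up the 30–90 missing children at 1.5 per household takes 20–60 further child-containing households per site and survey. Accepting 210 instead widens the simple binomial half-width at 50% prevalence from 1.96 × √(0.25/300) = 5.7 points to 1.96 × √(0.25/210) = 6.8 points. If the 1.5 is already an average over all households, deletion costs nothing.

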### 5.1.2 Screening of respondents.

When a household with at least one household adult resident is identified, study personnel will briefly describe the purpose of the study to the head of the household or any adult household member present at home in the appropriate language (usually Luganda or Lusoga for those in Walukuba; Rukiga or Runyankore for those in Kihihi, and Japadhola and Ateso for those in Nagongera sub-county). The inclusion criteria are: 1) Usual resident who is present in the sampled household on the night before the survey, 2) adult aged 18 years or older, 3) agreement to provide informed consent. The exclusion criterion are: 1) no adult resident home on more than 3 occasions, 2) household vacant, 3) dwelling destroyed or not found

### 5.1.3 Informed consent

Study personnel will conduct the informed consent discussion in the appropriate language and a translator will be used if necessary. The consent form will be available in English and the local languages (Appendix 1). Following the informed consent discussion, the respondent will be asked by the study personnel to sign a written consent form to participate in a research study. If the respondent is unable to read or write, their fingerprint will substitute for a signature, and a signature from a witness to the informed consent procedures will be obtained.

### 5.1.4 Household survey questionnaire

The household questionnaire (appendix 9) will be administered to the head of the household or their designate after obtaining their consent using a hand-held computer (paperless system). The questionnaire is based on the model Malaria Indicator Survey questionnaire developed by the Roll Back Malaria Monitoring and Evaluation Reference Group, as well as other questionnaires from previous surveys conducted in Uganda, including the 2006 Uganda Demographic and Health Survey (UDHS) and the 2009 and 2010 Malaria Indicator Survey.

The Household Questionnaire will obtain information on all residents in the selected households. Some basic information will be collected on the characteristics of each person listed, including age, sex, and relationship to the head of the household. Demographic information from the Household Questionnaire will be used to identify women who are eligible for the individual women interviews and those eligible for the clinical survey. The Household Questionnaire will also be used to collect information on indicators of ownership and use of mosquito bed nets. It will also collect proxy indicators of wealth based on responses of household’s dwelling unit, ownership of various durable goods and land, and household food security.

## 5.2 Women’s survey.

### 5.2.1 Recruitment of participants

The women’s survey targets all women of child-bearing age (15-49 years). The women shall be recruited from every household selected for the household survey.

### 5.2.2 Screening of participants

During the household survey interview, information is obtained on all residents in the selected households. The demographic information from the Household Questionnaire will be used to identify women who are eligible for the individual women interviews. Eligible women will be approached by study personnel who will briefly describe the purpose of the study to them in the appropriate language. The study inclusion criteria is: 1) usual female resident who is present in the sampled household on the night before the survey, 2) age 15 – 49 years, 3) agreement to provide informed consent (for adult women 18 years and above), 4) agreement to provide assent to participate in the study (for women aged 15-17 years), 5) agreement of parents or guardians of women aged 15-17 years to provide informed consent. The exclusion criterion is: 1) inability to locate on more than 3 occasions

### 5.2.3 Informed consent

Study personnel will conduct the informed consent discussion in the appropriate language and a translator will be used if necessary. Consent forms will be available in English and the local languages. Following the informed consent discussion, women aged 18 years and older will be asked by the study personnel to sign a written consent form to participate in a research study (appendix 1). Written assent to participate in the study will also be obtained from women aged 15 – 17 years at the time of the screening (appendix 2). The head of the household or their designate shall provide a second approved consent for women aged 15-17 years to participate in the study (appendix 1). If the respondents are unable to read or write, their fingerprint will substitute for a signature, and a signature from a witness to the informed consent procedures will be obtained.

### 5.2.4 Women’s questionnaire

After obtaining consent from the eligible women, interviewers will administer the women’s questionnaire (appendix 10) using a hand-held computer. Face-to-face personal interviews using a structured standard questionnaire will be administered. The Woman’s Questionnaire will be used to collect information on background characteristics (age, education, etc.); intermittent preventive treatment for malaria; current pregnancy; and antimalarial treatment for children under five with recent fever. It will also collect information on knowledge about malaria and cost of treatment of children under five with fever. In addition, if any of the women has given birth, she will be questioned about the vital statistics of her children (date of birth of each child, whether the child is still alive, and the age of death for any dead child).

### 5.2.5 Verbal autopsy procedures

If during the interview a death of child under five years of age is noted to have occurred during the past 5 years from the date of the interview, a Verbal Autopsy interview will be conducted to ascertain the cause of death (appendix 11 + 12). The mother of the deceased child and any other persons who took care of the child during the illness that resulted in death of the child will be identified. The caretakers will be expected to remember, recollect and give an accurate account of the circumstances leading to the death, and the signs and symptoms of the illness. The interview will be conducted using the Verbal Autopsy questionnaire at the convenience of the caretakers. In the event that the mother/caretakers of the deceased child does not feel comfortable to take part in the interview at that time, an alternative date will be set for the interview and the house re-visited for that purpose.

Completed Verbal Autopsy questionnaires will be photocopied and distributed to two independent physicians. The physicians will first review the questionnaires and assign the cause or causes of death according to their clinical opinion (physician review). Causes of death will be classified as immediate, underlying, and contributory causes, according to ICD-10 guidelines. Discrepancies in diagnoses will be documented and reviewed by a third physician, and a consensus will be sought with the original two physicians. The causes of death will be assigned the appropriate ICD-10 codes by the physicians using a standardized coding list. Deaths attributable to malaria will be considering cases in which malaria was classified as either the underlying or contributory cause of death in different epidemiological settings.

## 5.3 Clinical survey

### 5.3.1 Recruitment of participants

In each selected household, a clinical survey shall be conducted on all children under fifteen years of age, and on one household member within the age category 15-24 years, 25-34 years, 35-44 years, 45-54 years, and > 55 years.

### 5.3.2 Screening of participants

At the end of the household questionnaire, the study personnel will discuss the clinical survey aspect of the study with the head of the household or their designate and adult household members present. Study personnel will briefly describe the purpose of the clinical study in the appropriate language. The inclusion criteria are: 1) Usual residents who are present in the sampled households on the night before the survey, 2) children under 15 years of age or selected household members aged 15 years or older, 3) agreement of parents or guardians of children to provide informed consent, 4) agreement of eligible adults to provide informed consent and 5) agreement of a child aged 8 years or older to provide assent. The exclusion criterion is: 1) inability to locate the child on more than 3 occasions, 2) inability to locate other eligible respondents on more than 3 occasions. All children under 15 years of age will be included for the clinical survey. One person in each of the age category 15-24 years, 25-34 years, 35-44 years, 45-54 years, and > 55 years shall be randomly selected for the clinical survey.

